### Statistical considerations

#### Sample size calculations

Based on the event rates of a previous all-comer trial performed with the Korean population, we predicted POCO rates of PtCr-EES and BP-BES to be 6 % and 6 % at 12 months after index PCI, respectively [11, 13, 28]. Using a non-inferiority log-rank design with a non-inferiority margin of 2 %, sampling ratio of PtCr-EES:BP-BES at 1:1, allowing 5 % withdrawal rate in each group for the 12 months, a total of 3384 patients would result in a power of at least 81 % power with a 1-sided α of 2.5 %. The expected number of events in the stent comparison arm will be 362 as a total.

Also, to demonstrate the second hypothesis that the reduced dose of prasugrel is non-inferior to the conventional group regarding MACE rates at 12 months, we assumed the MACE rates of the reduced dose group and the conventional dose group to be 7 % and 8 %, respectively [29]. Using a non-inferiority design, a non-inferiority margin of 2.5 %, a sampling ratio of reduced dose group:conventional dose group at 1:1, allowing 5 % withdrawal rate in each group for 12 months, we need total 2348 patients in a statistical power of 75 % with a 1-sided α of 2.5 %. The expected number of events in the antiplatelet comparison arm will be a total of 342.

We expect 30 % of ACS patients’ criteria (age ≥ 75 years, body weight < 60 kg, or history of transient ischemic attack or stroke) would be excluded in the prasugrel comparison, which results in a sample size of 2369. If the number of exclusion criteria in the prasugrel comparison exceeds our expected number, patient recruitment will be done until the number of patients in the prasugrel arm is 2348.

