### Outcome measurements and definitions

There are two primary endpoints in this study. In the stent comparison arm, the primary endpoint will be POCO, defined as a composite of all-cause death, nonfatal MI, and any repeat revascularization at 12 months. In the prasugrel dose comparison arm, the primary endpoint will be MACE, defined as a composite of all-cause death, nonfatal MI, ST, repeat revascularization, CVA, and BARC class ≥ 2 bleeding at 12 months. Revascularization is considered clinically driven with follow-up angiographic diameter stenosis ≥ 50 %, and at least one of the following: 1) history of recurrent angina pectoris, presumably related to the target vessel; 2) objective signs of ischemia at rest or during exercise testing (or equivalent), presumably related to the target vessel; 3) abnormal invasive functional diagnostic testing; or 4) target lesion or target vessel revascularization with ≥ 70 % diameter stenosis, even without aforementioned ischemic signs/symptoms [24, 25]. To reduce the chance of so-called “oculostenotic reflex,” whereby rates of repeated revascularization are disproportionately high, investigators will be recommended to perform a non-invasive stress test prior to the decision of the re-intervention of the target lesions as much as possible and they will adhere strictly to a clinically driven revascularization protocol. All clinical outcomes were defined according to the Academic Research Consortium (ARC) [25, 26]. All clinical events including revascularization will be independently adjudicated by an independent event adjudication committee, and only clinically driven revascularization will be coded as an event.

Secondary endpoints will be the individual components of the primary endpoints. In addition, POCO and MACE rate at 36 months, device-oriented composite endpoint (composite of cardiac death, target vessel MI, or target lesion revascularization), and acute procedure success (device, lesion and procedure) will be included as secondary endpoints. In prasugrel the comparison arm, adherence to the study dose of prasugrel, PRU value by VerifyNow P2Y12 at 1 month, 12 months, and the ratio of patients with the therapeutic range of P2Y12 reaction units (PRU, 86-238) will also be analyzed [27].

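### Stent comparison: 81 % power and 362 events do not follow from a 6 % POCO rate at 12 months in 3384 patients; 12-month power is about 67 %, or about 55 % on the log-rank scale

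*Protocol article*

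**What the plan says.** All the planning figures stand in the first paragraph of Sample size calculations in the protocol article:

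- Event rates: "we predicted POCO rates of PtCr-EES and BP-BES to be 6 % and 6 % at 12 months after index PCI, respectively".
- Test and margin: "Using a non-inferiority log-rank design with a non-inferiority margin of 2" %, with "sampling ratio of PtCr-EES:BP-BES at 1:1".
- Losses: "allowing 5 % withdrawal rate in each group for the 12 months".
- Result: "a total of 3384 patients would result in a power of at least 81 % power with a 1-sided α of 2.5" %.
- Events: "The expected number of events in the stent comparison arm will be 362 as a total".

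Outcome measurements and definitions sets the same horizon for the stent arm's primary endpoint: "defined as a composite of all-cause death, nonfatal MI, and any repeat revascularization at 12 months". POCO at 36 months is a secondary endpoint. Statistical analyses names Kaplan-Meier estimates with a log-rank test, but it defines non-inferiority as a difference in POCO rates below 2 % at a one-sided alpha of 2.5 %. The Limitations section discusses reduced power for the prasugrel arm only.

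**The concern.** The paragraph gives a 12-month event rate, a number of patients and an expected number of events, and the third does not follow from the first two. The event count is about 1.8 times what the assumed rate allows (362/203). The power of a log-rank design depends on the number of events, so a wrong event count means that the stated power is wrong too.

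This comparison sets the overall size of the trial. A reader who sees at least 81 % power here, and a disclosed weakness only in the prasugrel arm, will take the stent comparison to be adequately powered. If it is not, an inconclusive stent result is considerably more likely than the plan admits.

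**Working it through.** **Inputs** (Sample size calculations, except where noted): POCO 6 % v 6 % at 12 months; absolute margin 2 points, so 8 % v 6 % at the margin; 1:1 allocation, 1692 per arm; 5 % withdrawal over 12 months, leaving 1692 × 0.95 ≈ 1607 per arm; one-sided alpha 2.5 % (z = 1.960). The decision criterion, a rate difference below 2 %, comes from Statistical analyses.

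**1. Reproducing the plan's pair of figures.** Under proportional hazards, 8 % v 6 % corresponds to a hazard-ratio margin of ln(0.92)/ln(0.94) = 1.3476. The protocol gives no hazard-ratio margin; this is a conversion of its 2-point margin. By Schoenfeld's formula, the events needed for 81 % power are

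4 × (1.960 + 0.878)² / ln(1.3476)² = 362.0.

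So 362 events and 81 % power come from one consistent log-rank calculation.

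**2. Events that 12 months can supply.**

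- No losses: 3384 × 0.06 = 203.
- 5 % withdrawal spread over the year (exponential event and withdrawal times): 198.
- 5 % contributing nothing: 3384 × 0.95 × 0.06 = 193.
- Rate implied by the stated count: 362/3384 = 10.7 %.
- Patients needed for 362 events within 12 months, with withdrawal: about 6190.

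**3. Power at 12 months on the rate difference.** Power = Φ(0.02/SE − 1.960), with SE = √(2 × 0.06 × 0.94/n).

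- n = 1692: SE = 0.00816, 0.02/SE − 1.960 = 0.49, power 68.8 %.
- n = 1607: power 66.5 %.
- Kaplan-Meier difference with Greenwood variance and withdrawal: 67.6 %; simulation (4000 runs): 67.4 %.
- Constrained-null (Farrington-Manning) variance: 68.0 % with n = 1692, 65.8 % with n = 1607.
- One-sided alpha of 5 % with no losses, more lenient than the plan: 78.9 %, still short of 81 %.

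**4. Power at 12 months on the log-rank scale.** Power = Φ(ln(1.3476) × √D/2 − 1.960), for D events.

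| Events D | Power |
|---|---|
| 362 (stated) | 81.0 % |
| 203 | 56.6 % |
| 198 | 55.5 % (simulation 55.4 %) |
| 193 | 54.5 % |

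**5. Sensitivity to the common POCO rate** (rate difference, 1607 per arm): 5 % gives 74 %, 6 % gives 66.5 %, 7 % gives 60 % and 8 % gives 55 %.

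**6. Size needed for 81 % on the rate difference.** (1.960 + 0.878)² × 2 × 0.06 × 0.94/0.02² gives 2272 per arm, or 4544 evaluable patients, and about 4784 with 5 % loss.

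**7. Possible origin of 362.** Suppose 6 % is taken as an annual event rate with 5 % annual loss, and patients are followed to a common close: uniform accrual over 2 years (the Discussion plans enrolment within 2 years) plus 1 further year. This gives about 372 events and 82.0 % power, within 3 % of the stated count. It is an inference, because the protocol does not state the horizon of its calculation.

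**The case against.** The arithmetic in steps 1 to 4 is hard to dispute, but several points can fairly be made against reading too much into it.

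- **The origin of 362 is not documented.** A two-year average follow-up comes close but does not hit 362 exactly. This stands, so the explanation in step 7 is only a conjecture. The inconsistency does not depend on it.
- **No single figure is the true power.** The sample size paragraph names a log-rank design, while the analysis section defines non-inferiority as a rate difference. This also stands, and the power should be given with its scale. It does not help the plan: the rate difference is the more favourable of the two scales and still falls at least 12 points short (81 − 68.8).
- **Patients are followed for three years, so more events will accrue.** They will, but the primary hypothesis is tested at 12 months, and the rate and the withdrawal in the calculation are both tied to 12 months.
- **The real POCO rate might be near 10.7 %.** That abandons the stated 6 %. With a fixed 2-point margin, the power for the rate difference would then drop to about 47 % (SE = √(2 × 0.107 × 0.893/1692) = 0.0106).
- **Overstated power does not bias the estimate or raise the false-positive risk.** This is correct. The harm is limited to an understated chance of an inconclusive result.
- **The prasugrel paragraph shows a similar mismatch.** It states 342 events, against 2348 × 0.075 = 176 at 7 % and 8 %. That is a separate figure and does not excuse this one.

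**Conclusion.** The concern holds. With the protocol's own inputs, 3384 patients yield about 193 to 203 POCO events by 12 months, not 362, and the stated 81 % power rests on the larger count. Power for the 12-month comparison is 66.5 to 68.8 % on the rate-difference criterion. It is about 54 to 57 % on the log-rank scale, if the 2-point margin is read as a hazard ratio of 1.348.

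These results assume 6 % in both arms, one-sided alpha of 2.5 % and withdrawal between zero and the stated 5 %. On the rate difference, about one truly non-inferior result in three would be missed. If both observed rates lie near 6 %, the observed difference would have to be below about 0.4 points to pass (0.02 − 1.960 × 0.00816 = 0.004). A positive conclusion, if reached, remains valid. Because the figure justifies the size of the trial for a primary hypothesis, it must be corrected.

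**What to change.** In Sample size calculations, state that 3384 patients give about 67 % power for the 12-month difference in POCO rates. If a hazard-ratio margin is really intended, state that margin and a power of about 55 to 57 %. Replace 362 by about 200 expected events at 12 months. If 362 was derived for a longer follow-up, give that horizon and its assumptions separately, and do not attach its power to the 12-month endpoint.

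Add the shortfall in the stent comparison to the Limitations section. In the same edit, check the 342 events stated for the prasugrel comparison against its 12-month rates.

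The cost is wording only. The endpoint, margin, alpha and number of patients stay as they are; the stated power becomes less favourable. Keeping 81 % for the 12-month rate difference would instead take about 4784 patients, which is not requested here.

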#### Statistical analyses

All primary and secondary endpoints and serious adverse events will be analyzed after adjudication by a member of researchers or clinicians. All primary and secondary endpoints will be analyzed both on an intention-to-treat basis (all patients analyzed as part of their assigned treatment group), and per-protocol basis. For patients receiving multi-vessel PCI, the target lesion/vessel will be declared by the operator prior to the interventional procedure.

Primary endpoints will be analyzed firstly on an intention-to-treat basis (all patients analyzed as part of their assigned treatment group), and then, on a per-protocol basis at 12 months and 3 years after index procedure. The null hypothesis will be evaluated on a non-inferiority basis with Kaplan-Meier survival with the log rank test. Non-inferiority is defined by a 1-sided alpha of 2.5 % and a difference in net POCO rates of less than 2 % in the stent comparison arm and MACE rate of less than 2.5 % in the antiplatelet comparison arm. All primary and secondary endpoints will be analyzed on a per-patient basis. Events within the first month, the period receiving a 10-mg dose of prasugrel before taking the allocated prasugrel dose, will also be analyzed on an intention-to-treat basis. In addition, a landmark analysis will be performed at 1 month after index PCI, as a sensitivity analysis.

Device-oriented composite endpoint (target lesion failure: a composite of cardiac death, target-vessel MI, or target lesion revascularization) will be analyzed using the *χ*^2^-test and Kaplan-Meier survival with the log rank test. Other secondary endpoints including all-cause and cardiac death, target vessel/lesion revascularization, non-target vessel/lesion revascularization, any revascularization, target-vessel and all-cause (including non-target vessel) nonfatal MI, ST, stroke (ischemic or hemorrhagic), bleeding (BARC classification ≥ 2) will be analyzed using the *χ*^2^-test and Kaplan-Meier survival with the log rank test. Acute procedure success (device, lesion, and procedure) and adherence to study dose of drug (prasugrel) will be analyzed using the *χ*^2^-test. The baseline coronary angiographic characteristics will be analyzed on a per-lesion basis.

Patients who undergo VerifyNow P2Y12 assay will be also analyzed as a prespecified subgroup analysis. The PRU value will be analyzed using the *t* test n the conventional dose group versus reduced maintain dose group. The ratio of patients with a therapeutic PRU range (86–238 PRU) will be analyzed using the *χ*^2^-test.

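### Non-inferiority is defined as an absolute rate difference, but the named test is the log-rank test and no hazard-ratio margin links the two

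*Protocol article*

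**What the plan says.** In the protocol article, Statistical analyses names the test: "The null hypothesis will be evaluated on a non-inferiority basis with Kaplan-Meier survival with the log rank test". The next sentence gives the criterion: "Non-inferiority is defined by a 1-sided alpha of 2.5" %, together with "a difference in net POCO rates of less than 2 % in the stent comparison arm" and, for the prasugrel comparison, "MACE rate of less than 2.5 % in the antiplatelet comparison arm".

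Sample size calculations describes the stent comparison this way: "Using a non-inferiority log-rank design with a non-inferiority margin of 2" %. Its rate assumption is: "we predicted POCO rates of PtCr-EES and BP-BES to be 6 % and 6 % at 12 months after index PCI". That section gives 3384 patients, 362 events and at least 81 % power for the stent comparison. For prasugrel it gives assumed rates of 7 % (reduced dose) and 8 % (conventional dose), a 2.5 % margin, 2348 patients, 342 events and 75 % power.

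Neither section, nor Treatment of missing values, states a hazard-ratio margin, a shifted log-rank null or a confidence limit for the rate difference. On timing, Statistical analyses has the primary endpoints analysed by intention to treat and then "on a per-protocol basis at 12 months and 3 years after index procedure", and states the margins without a time. Outcome measurements and definitions makes 12 months primary and 36 months secondary.

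**The concern.** The margins are in percentage points of cumulative incidence. The log-rank statistic works on the hazard scale and, in its ordinary form, its null is equality of the curves. So the stated test does not address the stated criterion unless a conversion is supplied, and none is.

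At stake is which of two legitimate analyses decides each primary comparison: a confidence limit for the rate difference set against 2 or 2.5 points, or a log-rank test shifted to a hazard-ratio margin that someone must choose. They can disagree on the same data. The trial is open-label, so that choice should be fixed in writing before outcome data are seen. The power a reader should credit also depends on it.

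**Working it through.** **1. Reproduce the stated powers.** Under proportional hazards a margin of m points at control rate p is HR = ln(1 − p − m) / ln(1 − p). With D events, 1:1 allocation and equal true hazards, power = Φ(√D/2 × ln HR − 1.96).

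- Stent: HR = ln 0.92 / ln 0.94 = 1.348. With D = 362, √362/2 × ln 1.348 ≈ 2.84, so power = Φ(0.88) = 81.0 %.
- Prasugrel: HR = ln 0.895 / ln 0.92 = 1.330. With D = 342, √342/2 × ln 1.330 ≈ 2.64, so power = Φ(0.68) = 75.2 %.

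Both stated figures come back, so the sizing evidently used hazard-ratio margins of about 1.35 and 1.33. The prasugrel figure needs equal true hazards at 8 %. With the stated 7 % versus 8 % and the same margin, 342 events would give 97.5 %.

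**2. Compare the two scales for the stent margin.**

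| Control rate | HR equal to 2 points | Points equal to HR 1.348 |
|---|---|---|
| 4 % | 1.516 | 1.35 |
| 6 % | 1.348 | 2.00 |
| 8 % | 1.264 | – |
| 9 % | – | 2.93 |

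**3. A data set with opposite verdicts.** Suppose 4 % is observed in both stent arms, 1692 patients each (3384/2), with no loss.

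- Difference: SE = √(2 × 0.04 × 0.96 / 1692) = 0.00674. The upper limit is 1.96 × 0.00674 = 1.32 points, which is below 2: pass.
- Hazard ratio: 0.04 × 1692 = 67.7 events per arm, and SE(ln HR) ≈ √(2/67.7) = 0.172. The upper limit is exp(1.96 × 0.172) = 1.40, which is above 1.348: fail.

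**4. How often the verdicts differ.** Simulation: 4000 trials per scenario, N = 3384, 12-month follow-up, 5 % dropout.

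| True rates (new v control) | Rate-difference test passes | Shifted log-rank (HR 1.348) passes |
|---|---|---|
| 4 % v 4 % | 83.1 % | 40.8 % |
| 6 % v 6 % | 67.6 % | 55.6 % |
| 9 % v 9 % | 50.6 % | 71.6 % |
| 5.36 % v 4 % | 14.1 % | 2.6 % |
| 8 % v 6 % | 2.9 % | 3.0 % |

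The gap between the columns is a lower bound on how often the verdicts differ: at least 42 % of trials at 4 % v 4 %, and at least 12 % at the planned 6 % v 6 %. At the planned margin itself (8 % v 6 %) both tests hold close to the intended 2.5 %.

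**5. Power on the stated scale at 12 months.** Power = Φ((margin − true difference)/SE − 1.96), with SE = √[(p₁(1 − p₁) + p₂(1 − p₂))/n]. The second figure in each line has n reduced by 5 %.

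- Stent, 6 % v 6 %, n = 1692 per arm: SE = 0.00816 and 0.02/0.00816 = 2.45, so power is 68.8 %; 66.5 % with loss.
- Prasugrel, 7 % v 8 %, n = 1174 per arm: SE = 0.01087 and 0.035/0.01087 = 3.22, so power is 89.6 %; 88.1 % with loss.
- Prasugrel, 8 % v 8 %: SE = 0.01120 and 0.025/0.01120 = 2.23, so power is 60.7 %; 58.6 % with loss.

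The drop from 81 % for the stent comparison is not caused by choosing the difference scale. At 12 months, 6 % of 3384 is about 203 events (193 after 5 % loss), and the shifted log-rank then has only about 54-57 % power. The stated 362 events correspond to about two years of mean follow-up (assuming constant hazard).

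**The case against.** The best defence is that the text does not prescribe an ordinary test of equality. It frames the null as one of non-inferiority, calls the stent sizing a non-inferiority log-rank design and fixes a one-sided 2.5 % level. A log-rank test with a shifted null is standard and valid, and the reproduced powers suggest that this is what was meant. This stands: it would be wrong to say that a log-rank test cannot serve. It does not remove the mismatch, because the shifted null needs a hazard-ratio margin, none is stated, and the criterion that is stated is on the other scale.

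It also limits what may be inferred. A reader might conclude that a non-significant log-rank result would be taken as non-inferiority, which at a true difference equal to the margin would pass about 37 % of the time (stent) or 45 % (prasugrel). A reader might also take the criterion as a bare point-estimate rule, which would pass about 50 %. The arithmetic is right, but the document states neither rule, and its one-sided alpha points away from both.

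A third tempting reading is that the primary horizon is contradictory. It is not: Outcome measurements and definitions settles it at 12 months. Statistical analyses is only loosely worded when it lists 3 years and leaves the margins without a time.

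It is also fair to say that a condensed article may leave the variance estimator and interval construction to the analysis plan. Their absence is not the point here. The article states both a test and a criterion, and the two do not match.

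Finally, 2 points and HR 1.348 coincide at the planned 6 %. The margins do, but the verdicts can still differ there (step 4).

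**Conclusion.** The point holds as a mismatch between stated test and stated criterion in both primary comparisons. It is not shown that the plan would inflate the false non-inferiority rate, and the horizon is not in contradiction. What is shown is that two valid readings are open, that they can give opposite answers (1.32 points passes while HR 1.40 fails, with 4 % in both stent arms), and that nothing in the article says which one counts. The stated 81 % and 75 % belong to an unstated hazard-ratio reading. On the stated absolute scale at 12 months, the stent comparison has about 67-69 % power at N = 3384. The prasugrel comparison has about 88-90 % at N = 2348 if the assumed 7 % and 8 % hold, or about 59-61 % if both rates are 8 %.

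These results assume proportional hazards for the conversions, a normal approximation for the limits and powers, and 0 to 5 % loss. The 4 % and 9 % control rates are illustrations, not figures from the article.

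**What to change.** Replace the test sentence with a decision rule on the scale of the margins. Non-inferiority is shown if the upper limit of the one-sided 97.5 % confidence interval for the difference in 12-month Kaplan-Meier event rates is below 2.0 points for POCO (PtCr-EES minus BP-BES), or below 2.5 points for MACE (5 mg minus 10 mg). Report the log-rank test and hazard ratio as supportive. State that the margins apply at 12 months and that 3-year results are secondary. Explicit hazard-ratio margins for a shifted log-rank test would be an acceptable alternative, provided the absolute criterion is then dropped as the deciding rule.

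Restate power on the chosen scale, giving the prasugrel figure both for 7 % versus 8 % and for equal rates.

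The cost is wording in the protocol and analysis plan, plus a less favourable stated stent power. Kaplan-Meier rates are already planned, so no new data are needed, and no added patients are required.

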In this study, we will compare 2 different maintenance doses of prasugrel beyond 1 month after PCI: conventional dose of 10 mg versus a reduced dose of 5 mg of prasugrel in Asian patients with ACS undergoing PCI. All of the enrolled patients will receive the currently recommended loading dose of prasugrel (60 mg), and maintain a 10-mg daily dose for the first month. After 1-month clinical follow-up, patients will receive maintenance dosage randomly assigned after PCI (10 mg versus 5 mg). Dual antiplatelet therapy is recommended for at least 1 year. Clinical adverse events, including bleeding, will be compared at 1-year clinical follow-up.

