### Study design

This is a prospective, open-label, multicenter, randomized controlled trial with a 2 × 2 factorial design. The flow chart of patients is shown in Fig. 1. The 27 cardiovascular centers in Korea will participate in this trial. Clinical follow-up will occur at 1, 12, 24, 36 months after index procedure. Investigators may conduct this follow-up as telephone interviews or office visits. There will be no mandatory angiographic follow-up unless clinically necessary. Prasugrel on-treatment platelet reactivity will be measured by using VerifyNow P2Y12 assay (Accumetrics, San Diego, CA, USA) in the antiplatelet arm at index procedure and at 1-month, and 12-month follow-up for the pre-specified subgroup analysis.

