1. The patient has a known hypersensitivity or contraindication to any of the following medications: heparin, aspirin, clopidogrel, prasugrel, ticagrelor, biolimus, everolimus, contrast media (patients with documented sensitivity to contrast media (e.g. rash) who can be effectively premedicated with steroids and diphenhydramine] may be enrolled. Those with true anaphylaxis to prior contrast media, however, should not be enrolled)
2. Patients with active pathologic bleeding
3. Gastrointestinal or genitourinary bleeding within the prior 3 months, or major surgery within 2 months
4. Systemic (intravenous) biolimus, or everolimus use within 12 months
5. Woman of childbearing potential, unless a recent pregnancy test is negative, who possibly plans to become pregnant any time after enrollment into this study
6. History of bleeding diathesis, known coagulopathy (including heparin-induced thrombocytopenia), or will refuse blood transfusions
7. Non-cardiac co-morbid conditions are present with life expectancy < 1 year or that may result in protocol non-compliance (per site investigator’s medical judgment)

*TIA* transient ischemic attack

If all eligible criteria are met and written informed consent is provided, patients will be randomized 1:1 to either (a) PtCr-EES or (b) BP-BES group, and 1:1 to either (a) reduced dose of prasugrel (5 mg daily) or (b) the conventional dose (10 mg daily) group. Patients who meet the exclusion criteria of prasugrel (age ≥ 75 years, body weight < 60 kg, or history of transient ischemic attack or stroke) will be enrolled in stent comparison, but excluded from prasugrel comparison. To generate comparable groups relative to known and unknown risk factors, randomization will be independently conducted online (T&W Software, Seoul, Korea) via web-based application. All randomization will be balanced, stratified by participating center and allocated treatment groups. According to the consideration of calculated sample size to meet non-inferiority in each comparison arms, a total of 3384 patients from 22 centers in Korea will be planned to be enrolled.

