### Interventions with study device and drug

The treatment strategy will be determined by the study-certified interventional operator. It is recommended that each enrolling investigator review the most recently updated instructions for use (IFU) and assess the contraindications, warnings, and precaution sections for treating potential patients. Direct stenting or predilation, antithrombotic medications during the procedure, and use of glycoprotein IIb/IIIa inhibitors will be left to the operator’s discretion.

The PtCr-EES (Promus Premier^TM^) is available in diameters of 2.25, 2.5, 2.75, 3.0, 3.5 and 4.0 mm with lengths of 12, 16, 20, 24, 28, 32 and 38 mm (2.25 mm diameter not available for 38 mm lengths). The BP-BES (Biomatrix®, Biomatrix Flex®) is available in diameters of 2.25, 2.5, 2.75, 3.0, 3.5 and 4.0 mm with lengths of 8, 11, 14, 18, 24, 28, 33 and 36 mm (33 and 36 mm lengths not available for 2.25 and 4.0 mm of diameters). Another BP-BES (Nobori®) is available in diameters of 2.25, 2.5, 2.75, 3.0 and 3.5 mm with lengths of 8, 14, 18, 24 and 28 mm. The allocated stent from the randomization should be implanted in all lesions treated. However, other stents may be used in case of device failure or situations in which the operators decide considering the best interest of the patient. It is recommended to make two attempts to cross the lesion with the allocated stent before switching to another stent. Complete lesion coverage is recommended. In case of long lesions, stent overlap of 1 to 4 mm will be recommended per IFU. The use of intravascular ultrasound, fractional flow reserve or optical coherence tomography will be left to the clinician’s discretion.

All patients will receive 300 mg of aspirin and a loading dose of prasugrel intravenously before performing PCI. Patients excluded from antiplatelet comparison will receive other P2Y12 inhibitors including clopidogrel, and ticagrelor. Patients included in the antiplatelet comparison will maintain aspirin with 10 mg of prasugrel until 1-month follow-up. After a 1-month period, patients randomized to the conventional dose group will receive a 10-mg daily dose of prasugrel, and the reduced group will receive a 5-mg daily dose. Dual antiplatelet therapy will be recommended for at least 1 year. The antiplatelet agent, however, could be adjusted at the clinician’s discretion in patients with bleeding events.

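### The 12-month PRU comparison uses an unadjusted t test and ignores the 1-month PRU taken while both arms were on the same dose; the 1-month comparison itself carries no dose contrast

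*Protocol article*

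**What the plan says.** In the protocol article, Study design schedules VerifyNow measurements "in the antiplatelet arm at index procedure and at 1-month, and 12-month follow-up". Outcome measurements and definitions lists, for the prasugrel comparison, "PRU value by VerifyNow P2Y12 at 1 month, 12 months", together with the proportion of patients inside the 86–238 PRU range.

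Statistical analyses then names the methods. For the value itself: "The PRU value will be analyzed using the *t* test n the conventional dose group versus reduced maintain dose group". For the 86–238 range it names a chi-square test. Neither sentence gives a time point, and neither uses an earlier PRU value. Treatment of missing values adds that the primary analysis of the study endpoints is not covariate-adjusted.

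On dosing, Interventions with study device and drug says: "Patients included in the antiplatelet comparison will maintain aspirin with 10 mg of prasugrel until 1-month follow-up". The two doses diverge only after that visit. Statistical analyses describes the first month in the same way, as "the period receiving a 10-mg dose of prasugrel before taking the allocated prasugrel dose", and adds a 1-month landmark analysis of clinical events as a sensitivity analysis.

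**The concern.** PRU is the trial's direct pharmacodynamic reading of the dose reduction, and two features of its analysis fit poorly with the design.

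First, if the t test is applied at each listed time point, the 1-month test compares 10 mg with 10 mg. A nominally significant result there would appear under a secondary outcome of the dose comparison without any difference in dose to explain it. For clinical events the plan deals with the common-dose month through the landmark analysis; for PRU it has no counterpart.

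Second, the comparison that does carry the dose contrast, at 12 months, discards a measurement made with the same assay in the same patients while both arms were on a common dose. A repeated laboratory value of this kind is usually among the best available predictors of the later one. Leaving it out costs precision in what may be only a subset of the randomised patients, namely those who have the assay.

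**Working it through.** The article gives no sample size, SD, effect size or power for PRU, so there is no stated figure to reproduce. The check has two parts.

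**Dose contrast at each time point**

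| Visit | Reduced group | Conventional group | Contrast |
|---|---|---|---|
| 1 month (before the change) | 10 mg | 10 mg | none |
| 12 months | 5 mg | 10 mg | the randomised one |

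Only the 12-month value can show an effect of the maintenance dose.

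**Precision at 12 months**

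Inputs: 1:1 allocation (Study population and entry criteria: "1:1 to either (a) reduced dose of prasugrel (5 mg daily) or (b) the conventional dose (10 mg daily) group"); two-sided 5 % level (assumed); r, the within-arm correlation of 1-month and 12-month PRU (assumed, 0.3 to 0.7); equal variances and a common r in both arms (assumed).

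Formulas, relative to the plain t test:

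- variance with ANCOVA: 1 − r²
- variance with the simple change from 1 month: 2(1 − r)
- equivalent gain in sample size: 1/(1 − r²)
- power with ANCOVA when the t test has 80 %: Φ[(1.960 + 0.842)/√(1 − r²) − 1.960]

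| r | ANCOVA variance | Change-score variance | Sample-size gain | Power if t test has 80 % |
|---|---|---|---|---|
| 0.3 | 0.91 | 1.40 | 1.10 | 83.6 % |
| 0.5 | 0.75 | 1.00 | 1.33 | 89.9 % |
| 0.7 | 0.51 | 0.60 | 1.96 | 97.5 % |

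Worked line for r = 0.5: 1 − 0.25 = 0.75; √0.75 = 0.866; 2.802/0.866 = 3.235; 3.235 − 1.960 = 1.275; Φ(1.275) = 0.899.

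As an illustration, an effect of 0.2 SD at 80 % power needs 393 patients per arm with the t test. With ANCOVA this becomes 393 × 0.91 = 358, 393 × 0.75 = 295 or 393 × 0.51 = 201, rounded up.

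**Simulation check** (200 per arm, 4,000 runs for each r, normal data, no arm difference at 1 month by construction)

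- With no 12-month effect, the 12-month t test rejects in 5.1 % to 5.4 % of runs and ANCOVA in 4.9 % to 5.2 %. Both hold their level.
- With a 12-month effect of 0.25 SD, the t test has about 70 % power. ANCOVA has 73 %, 83 % and 93 % at r = 0.3, 0.5 and 0.7.
- The 1-month test rejects in about 5 % of runs whether or not there is a 12-month effect.

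The change-score column shows why the remedy is ANCOVA: below r = 0.5 a change from 1 month is less precise than the t test it would replace.

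**The case against.** The strongest reply is that nothing here is invalid. A t test between randomised groups is unbiased and holds its level, and PRU is a secondary measure with no stated hypothesis or power. That stands in full. Chance imbalance at 1 month is no separate fault either, since the t test's standard error already allows for it. What remains is avoidable imprecision.

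A reader might infer that the plan commits to testing 1-month PRU as a dose effect. The article does not say so. The t-test sentence names no visit, and the outcome list says only that the 1-month and 12-month values are analysed. Testing at both visits is the natural reading, but it joins two sections.

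A reader might also call the 1-month PRU a pre-treatment baseline in which only chance differences can arise. That goes too far. It is measured after randomisation in an open-label trial, so knowledge of the assignment could affect adherence, early switching or attendance for the assay. It can serve as a covariate because the assigned dose is the same in both arms up to that visit, not because it precedes randomisation. For the same reason a 1-month comparison has some use as a check of comparability.

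Lastly, adjustment may be set out in an analysis plan that is not shown, and the article states that primary analyses of the endpoints are unadjusted. That sentence does not exclude an adjusted analysis of PRU, but the t test is the method that the article itself fixes, and it can be improved.

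**Conclusion.** The point holds as a low-cost improvement of minor weight. A 1-month comparison of PRU between arms carries no dose contrast. The 12-month t test is valid but gives up precision: 9 % of the variance at r = 0.3, 25 % at r = 0.5, 49 % at r = 0.7. These figures rest on an assumed correlation and on similar variances and slopes in the two arms. At the low end the gain is modest, and without a sample size or target effect for PRU the 12-month comparison cannot be called underpowered.

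The documents do not support a claim of bias or inflated type I error, and nothing here touches the primary non-inferiority tests of POCO or MACE.

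**What to change.** State the following before the PRU data are analysed:

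1. 12-month PRU is the dose comparison. Analyse it by ANCOVA with dose group and 1-month PRU as covariate, and keep the unadjusted t test as a sensitivity analysis. Note the exception beside the sentence on unadjusted analyses in Treatment of missing values.
2. The 1-month sample used as covariate must be drawn before the dose change.
3. Report 1-month PRU by arm descriptively, as a check that the arms are alike, not as a test of dose.
4. For the 86–238 range at 12 months, keep the chi-square test. If an analysis adjusted for 1-month PRU is added, report a standardised risk difference. Logistic regression alone gives a conditional odds ratio, which is a different quantity from the difference in proportions.
5. Fix in advance how patients with a 12-month but no 1-month value are handled, and report this missingness by arm. A missing-value indicator is less safe here than for a true baseline, because missingness after randomisation in an open-label trial may differ between arms. Use the index-procedure PRU as an alternative covariate, or the unadjusted analysis, as a check.

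The cost is wording. All three PRU measurements are already scheduled, so no new data are needed. The main drawback is the reliance on a post-randomisation covariate, which items 2 and 5 are meant to contain.
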